## Abstract

**Introduction:**

Drug-related problems (DRPs) are a major cause of unplanned hospital admissions among elderly people, and transitions of care have been emphasised as a key area for improving patient safety. We have designed a complex clinical pharmacist intervention that targets people ≥75 years of age undergoing transitions of care from hospital to home and primary care. The main objective is to investigate if the intervention can reduce the risk of unplanned drug-related readmission within the first 180 days after the person is discharged from hospital.

**Methods and analysis:**

This is a randomised, controlled, superiority trial with two parallel arms. A total of 700 people ≥75 years will be assigned to either intervention or routine care (control). The intervention, which aims to find and manage DRPs, is initiated within a week of the person being discharged from hospital and combines repeated medical chart reviews, phone interviews and in some cases medication reviews. People in both study arms may have been the subject of a medication review during their ward stay. As the primary outcome, we will measure time until unplanned drug-related readmission within 180 days of leaving hospital and use log rank tests and Cox proportional hazard models to analyse differences between the groups. Further investigations of subgroup effects and adjustments of the regression models will be based on heart failure and cognitive impairment as prognostic factors.

**Ethics and dissemination:**

The study has been approved by the Regional Ethical Review Board in Umeå (registration numbers 2017-69-31M, 2018-83-32M and 2018-254-32M). We intend to publish the results with open access in international peer-reviewed journals and present our findings at international conferences. The trial is expected to result in more than one published article and form part of two PhD theses.

**Trial registration number:**

NCT03671629

Strengths and limitations of this studyOne of few multifaceted clinical pharmacist interventions directed at transitions of care.Targets elderly people ≥75 years of age, a vulnerable group rarely addressed in clinical research.Conducted in a setting where medication reviews by clinical pharmacists are already implemented during routine hospital care.The participants are not blinded to the treatment assignments.

## Introduction

An ageing population with multiple morbidities and medications brings with it considerable challenges for healthcare and society in terms of adverse drug reactions and other drug-related problems (DRPs).^1^ Hospital admission rates increase with age and,^2–4^ although prevalence estimates differ between studies,^5^ it has been observed that up to 30% of unplanned hospitalisations among the elderly are caused by DRPs,^6 7^ a percentage that appears to be even higher in the vulnerable subgroup of old people with major neurocognitive disorder (NCD).^8^ The transition of care between different healthcare providers has been associated with a high risk of inappropriate prescribing, medication errors and adverse drug events,^9–11^ and the World Health Organisation (WHO) has identified transitions of care as a key issue for improving patient safety in primary healthcare.^12^

Poor medication adherence is a major concern in developed countries given that adherence rates average 50% among people with long-term therapies.^13^ The mechanisms of adherence are multifactorial and, even though there is little evidence to support old age alone as an independent predictor of non-adherent behaviour, the elderly are still at higher risk due to multiple morbid conditions and polypharmacy.^14^ Importantly, it has also been observed that even milder forms of cognitive impairment severely affect adherence to medication.^15^ In the context of transitions of care, poor adherence in the sensitive postdischarge phase has been associated with hospital readmission and appears to be of particular clinical relevance among people suffering heart failure.^16–18^

The clinical pharmacist is one of many professions involved in preventing and managing DRPs. In principle, clinical pharmacy can be described as the science and practice of rational medication use and includes both medication reviews and counselling with patients as well as other healthcare professionals.^19^ Medication reviews conducted by clinical pharmacists have demonstrated a positive overall effect on both the appropriateness and cost of medication.^20 21^ Regarding the effect on hospital readmissions and other clinical outcomes, review data are less consistent and incorporate few randomised controlled trials (RCTs)^22–24^; however, there are relatively recent findings indicating that medication reviews conducted by clinical pharmacists on the ward can reduce drug-related readmissions to hospital in various groups of elderly people.^25–27^ Postdischarge interventions involving phone-based follow-ups by clinical pharmacists have reduced all-cause readmission rates, but these trials did not specifically target an elderly population.^28 29^ In addition, there seems to be a need for more RCTs that target medication discrepancies and errors during care transitions between hospital and primary care.^30^ In summary, there is still insufficient evidence for an optimal postdischarge intervention model that incorporates adherence elements and specifically addresses transitions of care involving elderly people.

In the present study, our primary aim is to investigate the effect of clinical pharmacists in transitional care on unplanned drug-related readmissions among people ≥75 years of age in a context where medication reviews conducted by clinical pharmacists within the hospital are already common practice. Our primary objective is to assess if intervention by a clinical pharmacist during a transition of care can reduce the risk of unplanned drug-related hospital readmission for 180 days after the person leaves the hospital. As secondary objectives, we will study the effects of the intervention on unplanned drug-related readmissions within 30 days, unplanned hospital visits (all-cause readmissions and emergency department visits), mortality, medication adherence and quality of life. Subgroup analyses will be based on the occurrence of heart failure and cognitive impairment. Moreover, we will collect qualitative interview data regarding the intervention.

## Methods and analysis

### Principal study design

This study is conducted as a randomised, controlled, superiority trial with two parallel groups. The control group will be assigned to routine care while the intervention group will receive an extended clinical pharmacist service for a period of 180 days, a procedure that incorporates regular medical chart reviews, medication interviews, medication reviews (table 1) and collaboration with the primary care physician to address DRPs. It should be noted that study participants in both groups may already have been the subject of a medication review performed by a clinical pharmacist during their hospital stay.

**Table 1 T1:** Important aspects of the medication reviews conducted by clinical pharmacists employed by Region Västerbotten

Medication reconciliation	The pharmacist ensures that the medication records are updated and accurate. This assessment is based on both hospital and primary care medical records
Overall review of list of medications	This includes indications for therapies, correct choice of drugs, dosages, treatment durations and untreated indications
Clinical symptoms in relation to drug treatment	Symptoms of ADRs
Impaired body function	Liver and renal function, swallowing difficulties, contraindications and allergies
Drugs that require specific attention	Toxic drugs, drugs commonly associated with side effects and PIMs
Interactions	Drug–drug interactions and drug–food interactions

ADR, adverse drug reaction; PIM, potentially inappropriate medication.

### Study population, recruitment and randomisation

The recruitment of study participants started in September 2019 and takes place among emergency admissions to the University Hospital of Umeå. We will continuously recruit participants until we reach the target sample size of 700 randomised individuals. Thus far, recruitment has been limited to one medical ward; however, it is possible to increase the number of wards if the inclusion rate proves insufficient to reach the target sample size during 2022. People who meet the eligibility criteria are given the opportunity to participate in the trial (box 1). Once written consent has been obtained (approval from next of kin in cases of people with major NCD), the participants report self-assessed adherence and quality of life through questionnaires. Following discharge from the ward, the participants are randomly assigned to one of the two study arms through a stratified randomisation procedure (figure 1) based on their results from a shortened 4-item version of the Gottfries’ Cognitive Scale,^31^ a validated tool for proxy rating cognitive impairment.^32 33^ Within each stratum, the participants are further assigned to either of the study arms with an intended ratio of 1:1 through random allocation.

Box 1List of eligibility criteriaInclusion criteria≥75 years.Living at home (ie not in nursing home).Emergency admission.Registered at one of nine specified primary care centres.Exclusion criteriaDo not speak Swedish or unable to communicate.Admitted due to intoxication (drug or alcohol).Scheduled for palliative care.

**Figure 1 F1:**
[figure not shown]
Study flow chart from recruitment to final follow-up.

### Allocation concealment and blinding

We enrol participants before they are discharged from hospital. The allocation sequences are computer generated and managed by external administrators who irreversibly assign the participants to their respective treatments. From this stage onwards, the clinical pharmacists are aware of the group assignments. Study participants are considered blinded until the first phone call. The statistical analysis will be performed in agreement with a statistician who is unaware of the assigned treatments. All information about group assignments will also be unknown to the outcome assessors and any notes in medical records that might offer such clues will be removed beforehand.

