In addition to the prescheduled interviews, the intervention includes repeated medical chart reviews performed on average every second week during a period of 180 days after the participants have been discharged from hospital. This activity is implemented in order to identify discrepancies between the lists of medications before, during and after hospitalisation, unanswered referrals between healthcare providers, deviating laboratory values and whether the participant has had any relevant contacts with the healthcare system (figure 2). Moreover, the medical chart reviews also function as an important basis for the interviews. In the event of multiple medication alterations or any documented signs or symptoms that might be drug-related, the clinical pharmacist conducts a medication review (table 1). This process includes several steps, such as medication reconciliation, evaluation of proper dosage and indication, signs of ADRs or side effects, check for interactions and special considerations due to impaired renal function. In brief, the exact types of DRPs can differ considerably between participants and range from administration issues and poor medication adherence to drug-induced electrolyte imbalance or orthostatic hypotension. Identified or suspected DRPs that are detected through the interviews or medical chart reviews but cannot be solved by direct communication with the participant or next of kin are instead communicated over phone with the primary care physician. In this dialogue, the clinical pharmacist describes the potential DRP being present and offers a recommendation on how to manage the issue. The physician is the person who ultimately decides on any changes to medication regimens, in which case the clinical pharmacist contacts the patient within a few days in order to confirm and reinforce the physician’s instructions. All clinical pharmacists involved in the trial have electronic access to the participants’ medical charts. This access includes physicians’ notes, laboratory records, current lists of medications and epicrises. The combined information from these sources provide a basis for both medical chart reviews and medication reviews. During the intervention, the clinical pharmacist continuously documents the time spent on the different activities for each participant.

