### Data collection and outcomes

All outcome data will be gathered from medical charts with the exception of self-report questionnaires. All collected research data will be coded and kept in locked archives. Before, during and after the trial, all forms and protocols used during the interventions and follow-ups that reveal individual personal data are stored according to the same principle. There will be no identifiable data in the dissemination of the results. In summary, outcomes will be measured at the time of discharge from hospital (baseline) and then after 30 and 180 days, respectively (table 2). The follow-ups on Medication Adherence Report Scale (MARS-5) and EuroQuol five-dimension (EQ-5D) are conducted by phone and preferably in conjunction with the intervention phone calls. Rehabilitation needs require that some enrolled participants are transferred to the geriatric department before leaving the hospital for home. If a participant is relocated to another clinical ward, the actual discharge from hospital will be considered as baseline, with the exception of self-reported adherence and quality of life, which are reported on the original ward. As a consequence, we contact all study participants by phone at 30 and 180 days after their first report regarding MARS-5 and EQ-5D, even if this date differs from the actual date on which they were discharged from hospital.

**Table 2 T2:** Scheduled data collection for primary and secondary outcomes

	Baseline	30 days	180 days

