#### Hospital readmissions

The primary outcome is time until unplanned drug-related readmission within 180 days of being discharged from the hospital. As a secondary outcome, we also study these events within a narrower time frame of 30 days. The cause of each readmission will be retrospectively determined by a group of blinded physicians and pharmacists who are not otherwise involved in the study. This assessment group will reach a consensus decision regarding the causality of each readmission according to criteria from WHO, a method that has been used previously in similar studies.^25 34 35^ Readmissions classified as certain, probable or possible in this assessment will be regarded as drug related in the following statistical analysis. We also measure time until unplanned hospital visit (all-cause readmissions and emergency department visits), time until death, as well as frequencies of unplanned drug-related hospital readmissions and unplanned hospital visits.

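### Removing notes that hint at the arm before the primary endpoint is adjudicated risks unequal evidence between arms; a uniform file with identifying words masked would be safer

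*Protocol article*

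**What the plan says.** Under *Allocation concealment and blinding*, the protocol article keeps group assignment from the outcome assessors and adds that "any notes in medical records that might offer such clues will be removed beforehand". The unit of removal is the note, and the trigger is that it hints at the arm.

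*Data collection and outcomes* gives the source: "All outcome data will be gathered from medical charts with the exception of self-report questionnaires". *Hospital readmissions* describes the judgement: "The cause of each readmission will be retrospectively determined by a group of blinded physicians and pharmacists who are not otherwise involved in the study". The group decides by consensus on WHO criteria, and the threshold is low: "Readmissions classified as certain, probable or possible in this assessment will be regarded as drug related in the following statistical analysis".

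*Intervention group protocol* describes what happens in the intervention arm only. There are phone interviews on side effects, adherence and other drug problems, and "repeated medical chart reviews performed on average every second week during a period of 180 days". A medication review follows when findings call for it. Problems that cannot be settled with the participant or next of kin "are instead communicated over phone with the primary care physician". In that call "the clinical pharmacist describes the potential DRP being present and offers a recommendation on how to manage the issue", and the physician then decides on any change.

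**The concern.** A rule that acts on clues to the arm acts on whatever generates the clues. Here that is the intervention itself: pharmacist contact about drug problems after discharge. The notes most likely to be removed are therefore concentrated in one arm and concern the subject that the assessors must judge.

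The sharpest case is the physician's own record. Suppose a primary care physician changes a drug because of a suspected side effect and writes that this followed a call from the study pharmacist. The entry hints at the arm and falls under the rule. A control physician who finds the same problem unaided writes a similar entry, and it stays. A readmission note that mentions the pharmacist is exposed in the same way.

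The stake is the primary endpoint. *Limitations and risk of bias* notes that two of the authors also deliver the intervention, relies on external assessment of the primary outcome, and concludes that the resulting risk of bias mainly concerns the two questionnaires. That reassurance is weaker if the assessors' source material differs by arm.

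**Working it through.** **Where clues to the arm can arise**

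1. *In-hospital pharmacist reviews.* Either arm may have had one (*Principal study design*). Randomisation follows discharge (*Study population, recruitment and randomisation*), so a review during the index stay cannot reveal the arm.
2. *Trial phone calls to controls.* The questionnaires are repeated by phone in all participants at 30 and 180 days (*Data collection and outcomes*). A record of such a call does not by itself reveal the arm, although its content might.
3. *Post-discharge pharmacist notes.* If charted, these exist in the intervention arm alone. Removing them makes the two charts more alike.
4. *Physician entries that mention the pharmacist.* The clinical content (symptom, suspected drug, change) has a counterpart in control charts. Removing the whole entry takes that content from one arm only.

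Item 4 is where the rule can produce an imbalance.

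**The plan's own figure**

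Inputs from *Statistics*: 19% in controls, a 40% relative reduction, 80% power, two-sided 0.05. Allocation is 1:1. With the exact 40% reduction, p2 = 0.19 × 0.60 = 0.114 and the mean is 0.152:

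n per arm = [1.960 × √(2 × 0.152 × 0.848) + 0.842 × √(0.19 × 0.81 + 0.114 × 0.886)]² / 0.076²

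= [0.995 + 0.425]² / 0.005776 ≈ 349.1, so 350 per arm and 700 in total.

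The stated 700 reproduces (power 80.1%). The rounded 11% would give 624. The sample size is not in question; the two-proportion approximation is reused below.

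**Illustration of one-arm loss (assumed; the document gives no misclassification rate)**

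Let both arms have a true rate of 19%, and let a share m of drug-related readmissions in the intervention arm be graded not drug related. The observed rate there is 0.19 × (1 − m). For m = 10%:

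- Observed rate: 0.19 × 0.90 = 0.171, a difference of 0.019. With 350 × 0.19 = 66.5 expected events, the loss is about 6.7 events.
- SE under the null: √(2 × 0.1805 × 0.8195 / 350) = 0.02907. SE under the alternative: √((0.19 × 0.81 + 0.171 × 0.829) / 350) = 0.02906.
- Rejection favouring the intervention: Φ[(0.019 − 1.96 × 0.02907) / 0.02906] = Φ(−1.31) = 0.096.
- Rejection in the other direction: Φ[(−0.019 − 1.96 × 0.02907) / 0.02906] = Φ(−2.61) = 0.004.
- Two-sided total: about 0.100, against a nominal 0.05.

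| Assumed loss m | Observed rate | P(significant, favouring intervention) |
|---|---|---|
| 0 | 19.0% | 2.5% |
| 5% | 18.05% | 5.1% |
| 10% | 17.1% | 9.6% |
| 20% | 15.2% | 26.6% |
| 30% | 13.3% | 53.6% |

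By symmetry, the same loss in the control arm would give the same probabilities against the intervention. If the true intervention rate were 11%, a 10% loss there would show 9.9%, and the apparent relative reduction would move from 1 − 0.11/0.19 = 42% to 1 − 0.099/0.19 = 48%.

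**The case against.** The strongest reply is that the article does not say clinical evidence is lost. It does not state whether whole entries or only identifying words go. It describes drug problems reaching the physician by phone and does not say that the pharmacist files interview findings or reviews in the chart. Pharmacist notes have no control counterpart, so leaving them in would unblind assessors and add drug-problem evidence to one arm. The assessors judge the readmission, and its admission note, laboratory values and drug list would normally remain. Operational detail may sit in a fuller protocol or adjudication manual. All-cause readmissions, emergency visits and mortality are also collected and need no causality judgement.

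Much of this stands. A reader might infer that drug-problem evidence is stripped from the intervention arm only, and that this favours the intervention. The document does not support that. It does not confine removal to one arm, and control charts could also hold a revealing entry. Nor is the direction fixed: thinner notes could lower the intervention arm's count, while the drug changes and laboratory follow-up that remain could raise it or give the arm away.

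Two things are not answered. The point rests on a rule that the article states, namely removal of notes, and not on detail it omits. And the argument that removal makes charts more alike does not reach physician entries, which exist in both arms. The unadjudicated outcomes are a useful check but do not repair the primary endpoint.

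**Conclusion.** The concern holds as a risk. A removal rule triggered by clues to the arm will act mainly on intervention charts, and it can take out a physician's entry on a drug problem while a comparable control entry remains. With *possible* as the lowest qualifying grade, modest differences in evidence could move cases across the line.

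Neither the size nor the direction of any bias can be derived from the document. The figure of about 10% two-sided rejection rests on an assumed 10% one-arm loss, 19% in both arms, 350 per arm and no true effect. At zero loss nothing changes. The illustration shows that the endpoint is sensitive to the loss of about seven events; it does not show that such a loss will occur. The point is best classed as a cheap improvement.

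**What to change.** Replace the removal of clue-bearing notes with an adjudication file of prespecified content:

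- The same document types for every readmission in both arms, centred on the index discharge records and the readmission records.
- Identifying words (the trial, the study pharmacist) masked within the text, with whole entries kept so that the clinical facts survive.
- The same procedure in both arms, carried out by someone who does not deliver the intervention. The administrators who manage allocation are not an obvious choice, since they may know the arm.
- One decision, made in advance and applied identically to both arms, on whether primary-care notes are included. Leaving them out removes many clues but also loses interim drug changes and symptoms that bear on causality; keeping them does the reverse.
- A report of the amount masked by arm and of each assessor's guess of the arm. A sensitivity analysis counting only certain and probable grades would show how far the result depends on the lowest one.

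Adjudication is retrospective and 161 of 700 participants had been randomised by November 2019, so one procedure can still cover everyone. The cost is somewhat more file preparation. Some risk of unmasking remains, because drug lists and laboratory follow-up may themselves hint at the arm.
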